### Site selection and randomization

Study sites were selected from among secondary- and tertiary-level PEPFAR-supported healthcare facilities with at least 12 months’ experience in providing comprehensive HIV care and treatment services. Eligible sites were further expected to meet the following criteria:At least 20 ALHIV enrolled in care as of 31 July 2016Separate pediatric and adult HIV care teams and clinicsAt least one dedicated physician and one dedicated nurse for each pediatric and adult HIV clinic

All sites were assessed using a standardized tool to determine whether they met the selection criteria.

Our desire was to meet the suggestions of the Consolidated Standards of Reporting Trials (CONSORT) “extension for cluster designs” checklist in our randomization procedure. To that end, we provide details here of both sequence generation and allocation [29]. Twelve healthcare facilities were selected and randomized 1:1 to the intervention and control arms (Fig. 2). These 12 study sites were pair-matched by geographic location and level of care and then randomly assigned to the intervention group (IG) or to the control group (CG). Particular attention was paid to remove bias of group assignment by concealment at the individual participant level. The randomization of facilities was carried out using scripting language in R (v. 3.3.2) by the project statistician [30]. We first created a random number between 1000 and 10,000 and used the result to seed the group assignment so that the results would be reproducible. Based on the pair-matched locations and level of care, we used the “sample” function to determine which member of each matched facility pair would be assigned to each of CG and IG. Of note, age at transfer for each study site was considered in order to include sites that transferred at 15 years as well as 18 years, according to the results of our survey [14]. All enrolled study participants receiving care at each study site will follow the procedures of their respective randomization arms described below.

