### Data collection

After obtaining informed consent and/or assent, research assistants will collect sociodemographic and medical history information onto enrollment forms by face-to-face interview with study participants and/or their caregivers. Four psychosocial health questionnaires (described below) will also be completed at enrollment by study participants. Completion of the four questionnaires will be repeated at 12, 18, 24, and 36 months after enrollment, coinciding with the transfer time point, and 6, 12, and 24 months post transfer, respectively (Table 1). Blood viral-load sampling will be performed on the same schedule, and the results of all viral-load tests will be reported to clinic providers and filed in participants’ medical charts for use in HIV management. Per national treatment guidelines, stable patients who have been on HIV treatment for at least 6 months should have at least one viral-load test every year [31]. Clinic visits will also be tracked to measure the primary outcome of retention in care.

**Table 1 Tab1:** Adolescent Coordinated Transition (ACT) study timeline, visits, and procedures

Visit	Timeline	Study visit	Procedure	Intervention group	Control group
Enrollment	0 months	Yes	Enrollment	Yes	Yes
			Readiness assessment	Yes	Yes
			Psychosocial assessment^a^	Yes	Yes
			Viral load	Yes	Yes
Visit 1	3 months	Yes	Type of clinic	Pediatric clinic	Pediatric clinic
			Organized support group	Yes	No
			Readiness assessment	Yes	Yes
Visit 2	6 months	Yes	Type of clinic	Adult clinic	Pediatric clinic
			Organized support group	Yes	No
			Readiness assessment	Yes	Yes
Visit 3	9 months	Yes	Type of clinic	Pediatric clinic	Pediatric clinic
			Organized support group	Yes	No
			Readiness assessment	Yes	Yes
Visit 4	12 months	Yes	Type of clinic	Adult clinic	Pediatric clinic
			Organized support group	Yes	No
			Readiness assessment	Yes	Yes
			Viral load	Yes	Yes
Transfer to adult care					
Visit 5	15 months	No	Type of clinic	Adult clinic	Adult clinic
			Organized support group	Yes	No
Visit 6	18 months	Yes	Type of clinic	Adult clinic	Adult clinic
			Organized support group	Yes	No
			Viral load	Yes	Yes
Visit 7	21 months	No	Type of clinic	Adult clinic	Adult clinic
			Organized support group	Yes	No
Visit 8	24 months	Yes	Readiness assessment	Yes	Yes
			Psychosocial Assessment^a^	Yes	Yes
			Viral load	Yes	Yes
End Visit	36 months	Yes	Type of clinic	Adult clinic	Adult clinic
			Readiness assessment	Yes	Yes
			Psychosocial Assessment^a^	Yes	Yes

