### Outcome measures

The primary outcome measure is the *proportion of ALHIV retained in care at 12 and 24 months post transfer.* For this study, retention is defined as having made at least two clinic visits separated by a 6-month period within 12 months and at least four visits each separated by at least 6 months within 24 months post transfer. Hence, there are two primary outcome measures, with the long-term (24-month) retention measurement being a necessary “composite” of those who would have already demonstrated short-term (12-month) retention.

Secondary outcome measures are as follows:
*Proportion of ALHIV achieving viral suppression measured at 12 and 24 months post transfer*. Viral suppression is defined per the 2016 Nigerian national HIV guidelines as < 20 copies of HIV ribonucleic acid (RNA) per milliliter of blood plasma after at least 6 months of taking ART [33]
*Proportion of ALHIV demonstrating psychosocial wellbeing during study follow-up.* This study team has previously reported that poor psychosocial wellbeing and lack of adequate coping/self-efficacy skills are potential barriers to successful outcomes, including transitioning for this population in Nigeria [22, 34]. In order to generate more comprehensive evidence on wellbeing and resilience among ALHIV, we will administer four questionnaires among our study cohort: (1) the Health Locus of Control (HLC) scale will assess the extent to which ALHIV consider their health and health decisions to be within, or outside of their control; (2) the Mental Health Continuum-Short Form (MHC-SF) will measure the constructs of social, emotional, and psychological wellbeing; (3) the Functional Social Support Questionnaire (FSSQ) will evaluate the strength of the social support network of ALHIV; and (4) the psychosocial determinants of sexual risk behavior using the Sexual Risk Behavior, Beliefs, and Self-efficacy (SRBBS) scale will investigate for key psychosocial variables affecting ALHIV sexual risk-taking or protective behaviors [34–40]

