### Statistical analysis

For the primary objective, the study will assess the differential impact that the ACT intervention has on the primary outcome of retention. For this measure, ACT will test the difference in the percentage of study participants completing scheduled clinic visits under the hypothesis that the IG’s percentages will exceed CG percentages from baseline to 12 months (“short-term” retention) and to 24 months (“long-term” retention) following transfer to adult care. An initial test of proportions will be conducted at each time period to compare these percentages using a one-way test, and exact *p* values will be calculated using a permutation distribution. Additionally, a Poisson regression model with a time offset will be explored, which will allow for the development of a model to compare rates between the control and intervention arms while accounting for events (i.e., retention) per unit time, which allows time to vary for each subject as well as allowing the inclusion of potential covariates (for example, age, and time since HIV diagnosis).

Similarly, for secondary objective 1, the study will assess the differential impact that the intervention has on viral suppression. For this measure, ACT will test the difference in the percentage of study participants achieving viral suppression, under the hypothesis that the IG percentages will exceed CG percentages at each time period. The strategy in this analysis is similar to that of the primary objective: a one-way test of proportions will be conducted initially, followed by a Poisson count model to account for potential covariates of interest in addition to a temporal component.

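### The first comparison for viral suppression is an unadjusted test in adolescents already on ART, and the enrollment viral load is named in no stated analysis, at a cost in precision

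*Protocol article*

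**What the plan says.** The protocol article's Outcome measures section defines the outcome as "Proportion of ALHIV achieving viral suppression measured at 12 and 24 months post transfer", with suppression meaning fewer than 20 "copies of HIV ribonucleic acid (RNA) per milliliter of blood plasma after at least 6 months of taking ART". Being on ART at a study site is an inclusion criterion.

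Under Data collection, "Blood viral-load sampling will be performed on the same schedule" as the questionnaires, and Table 1 lists a viral load at enrollment in both arms.

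For secondary objective 1, the Statistical analysis section tests the difference in percentages "under the hypothesis that the IG percentages will exceed CG percentages at each time period". The method is that "a one-way test of proportions will be conducted initially, followed by a Poisson count model to account for potential covariates of interest" and a temporal component. The only covariate examples stand in the preceding paragraph, on retention, where the Poisson model is described as "allowing the inclusion of potential covariates (for example, age, and time since HIV diagnosis". Enrollment viral load is not named there or elsewhere in the analysis section. The psychosocial scores, by contrast, are analysed as change from a baseline, namely the transfer visit.

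On design: "Twelve healthcare facilities were selected and randomized 1:1 to the intervention and control arms", and "These 12 study sites were pair-matched by geographic location and level of care".

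**The concern.** In a cohort already on treatment, suppression at entry is likely to be a strong predictor of suppression two and three years later. Some participants will meet the definition on day 0; the document does not say how many. Only 12 sites were randomized and suppression was not a matching factor, so the arms can start some way apart by chance. Part of that gap will still be present at 12 and 24 months post transfer. A plain test of proportions cannot take account of it, although the value that would do so is already collected in both arms.

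At stake is the precision of the secondary comparison and how far its estimate can be trusted in the one allocation that was drawn. Covariate lists are often left to an analysis plan, but here the protocol itself makes the unadjusted test the first comparison.

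**Working it through.** **Inputs from the document.** Six sites per arm; 15 analysed per site; ICC 0.05; correlation among repeated measures 0.3 (Sample size estimation; not specific to viral load). The sample size chain reproduces: 15 × 0.22 = 3.3, taken as 3; 15 + 3 = 18 per site; 18 × 12 = 216. The analysed number per arm is 15 × 6 = 90. The document gives no figure for suppression at entry.

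**Assumptions.** Entry suppression p = 0.40 to 0.70. Follow-up suppression is either 0.80 if suppressed at entry and 0.40 if not, or 0.85 and 0.30, or set so that the within-person correlation is 0.3. No intervention effect; pair matching not modelled.

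**Step 1: chance gap at entry.** The design effect is 1 + 14 × 0.05 = 1.7, so SD(d0) = √[2p(1−p) × 1.7/90].
- p = 0.40: √(0.816/90) = 9.5 points
- p = 0.55: √(0.8415/90) = 9.7 points
- p = 0.70: √(0.714/90) = 8.9 points

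With 90 per arm, a gap above 10 points means a difference of at least 10 participants. The continuity-corrected cut is therefore 9.5/90 = 10.6 points. The two-sided normal probability is 27%, 27% and 24% respectively. Simulation with beta-distributed site rates gives 23-28%. Without the continuity correction, the normal figures are 26-30%.

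**Step 2: how much carries forward.** Let b be the follow-up suppression probability in those suppressed at entry minus that in those not suppressed. If follow-up depends on entry status alone, an entry gap of 10 points gives an expected follow-up gap of 10b: 3 points at b = 0.30, 4 at 0.40 and 5.5 at 0.55.

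**Step 3: variance removed by adjustment.** With p1 and p0 the two follow-up probabilities and b = p1 − p0, the share removed is b²Var(d0) / {b²Var(d0) + 2[p·p1(1−p1) + (1−p)·p0(1−p0)]/90}.
- p = 0.55, 0.80/0.40: 0.16 × 0.00935 = 0.00150; 2 × 0.196/90 = 0.00436; share 0.00150/0.00585 = 26%. The SD falls from 7.6 to 6.6 points.
- p = 0.55, 0.85/0.30: 0.3025 × 0.00935 = 0.00283; 2 × 0.1646/90 = 0.00366; share 0.00283/0.00649 = 44%. The SD falls from 8.1 to 6.0 points.
- Correlation ρ = 0.3, same rate at entry and follow-up: the formula reduces to 1.7ρ²/(1.7ρ² + 1 − ρ²) = 0.153/1.063 = 14%.

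Simulation, which also carries the small cost of estimating the slope, gives about 13-43% over these settings. At ρ = 0.3 the saving is 13-14%, and the SD falls by about half a point, from 7.0-7.6 to 6.5-7.1.

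**Step 4: bias.** In every simulated setting the mean unadjusted difference without an effect was 0 to within simulation error.

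**Sensitivity.** If a site's own suppression rate also persists over time, with 50-70% suppressed at entry and 30-70% of participants keeping their entry status, adjustment removes 29-68% of the variance. In the 12-15% of such trials where the intervention arm starts at least 10 points ahead, the spurious follow-up gap falls from 9-13 points to 2-4.

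**The case against.** The strongest reply is that the article is silent rather than wrong. The Poisson model for suppression is open to any covariate of interest. The age and time-since-diagnosis examples belong to the retention model, and a final covariate list is commonly left to an analysis plan, which is not at hand. This stands. A reader might infer that enrollment viral load is excluded, but the document supports only that it is not named. The reply does not reach the first-line test, which the protocol fixes as unadjusted.

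Second, a reader might infer that chance imbalance would be reported as an intervention effect, in other words that the comparison is biased. It is not: sites were randomized, the unadjusted difference averages zero when there is no effect, and a test that respects the clusters allows for chance imbalance in its error rate. In simulation, a one-sided 5% test of proportions rejects in about 10-11% of trials without an effect, but this comes from ignoring clustering, which is a separate matter.

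Third, a reader might call it an error to count maintained and newly gained suppression together. The outcome is defined as status at the visit, and the objective concerns suppression rates after transfer, so the pooled proportion is a legitimate target.

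Fourth, the size rests on assumed entry rates and persistence. The exclusion of participants who are not medically stable is not a virologic criterion, so it does not show that most are suppressed at entry. If location and level of care are related to suppression, pair matching would reduce the imbalance. Larger figures, such as a gap above 10 points in 39% of trials or 53% of variance removed, need an ICC of 0.10, twice the protocol's value. All of this stands and limits the claim to the ranges given here.

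**Conclusion.** The point holds as one of precision and of protection against an unlucky allocation, not of bias. A baseline measure of the outcome is collected in both arms, and the protocol's first comparison for secondary objective 1 makes no use of it. Under the stated assumptions at the protocol's ICC of 0.05, an entry gap above 10 points, in either direction, arises in roughly 23-28% of randomizations. Adjustment removes about 13% of the variance if the within-person correlation is 0.3, and up to about 43% if entry status persists more strongly. The benefit therefore runs from modest to substantial, and the document cannot say which. The outcome is secondary, but the improvement needs no new data, so the change should be made.

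**What to change.** State that the main comparison for secondary objective 1, at 12 and 24 months post transfer, comes from a model that respects the site clusters and adjusts for viral suppression at enrollment (below 20 copies/mL, yes or no) or for log10 enrollment viral load. Choose one of the two in advance. An unadjusted comparison can be kept as supportive.

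Specify the enrollment value as baseline. The psychosocial analysis uses the transfer visit, but by then the intervention arm has had a year of intervention, and adjusting for that value could remove part of a real effect.

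Say in the outcome definition that the measure is suppression status at the visit. Results by entry status (maintained or newly suppressed) may be added descriptively only: about 90 analysed participants per arm, split in two across six sites, give imprecise strata.

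The cost is a few sentences of analysis text. No additional sampling or visits are needed.

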**Methods:**

Using a two-arm cluster randomized control design, the Adolescent Coordinated Transition (ACT) trial will measure the comparative effectiveness of a graduated transition and organized support group intervention against the usual practice of abrupt transfer of Nigerian ALHIV from pediatric to adult care. This study will be conducted at 12 secondary and tertiary healthcare facilities (six intervention, six control) across all six of Nigeria’s geopolitical zones. The study population is 13- to 17-year-old ALHIV (*N* = 216, *n* = 108 per study arm) on antiretroviral therapy. Study participants will be followed through a 12-month pre-transfer/transition period and for an additional 24 months post transfer/transition. The primary outcome measure is the proportion of ALHIV retained in care at 12 and 24 months post transfer. Secondary outcome measures are proportions of ALHIV achieving viral suppression and demonstrating increased psychosocial wellbeing and self-efficacy measured by psychometric tests including health locus of control, functional social support, perceived mental health, and sexual risk and behavior.

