### Study objectives and hypotheses

This study’s primary objective is to measure the comparative effectiveness of the ACT intervention versus usual care on post-transfer retention in care among ALHIV at 12 and 24 months post transfer. The ACT intervention encompasses a graduated transition period coordinated with an organized support group, which aims to increase retention rates among ALHIV after transfer to adult care. The coordination denotes a complementary pediatric-adult team approach to support the clinical and psychosocial health of the transitioning ALHIV. The graduated transition provides an extended period of time for the transitioning ALHIV to become familiar with adult care while separating from pediatric care. A transition period, rather than abrupt transfer, minimizes the grief associated with the loss of the pediatric “family” and maximizes opportunities for the ALHIV and adult care providers to establish trusting relationships. The ACT intervention is to be compared to the usual care which is abrupt transfer of ALHIV to adult care with neither a transition period nor an organized support group.

ACT’s secondary objectives are:To measure the comparative effectiveness of the ACT intervention versus usual care on post-transfer viral suppression rates among ALHIV at 12 and 24 months post transferTo measure the comparative effectiveness of the ACT intervention versus usual care on psychosocial wellbeing as measured by psychometric tests at 12 and 24 months post transfer

We hypothesize that:Compared to those exposed to usual care, ALHIV exposed to the ACT intervention will have significantly higher rates of retention in careCompared to those exposed to usual care, ALHIV exposed to the ACT intervention will have significantly higher rates of viral suppression and higher scores on psychometric testing indicating better psychosocial wellbeing

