For secondary objective 2, the study will assess whether the ACT intervention leads to improvements in the social, emotional, and psychological wellbeing of study participants; improvements in their self-efficacy; or changes in their health locus of control (HLC) from an external to an internal locus of control. Additionally, ACT aims to understanding the potential of psychologically based intervening variables to influence important study outcomes (i.e., increased retention rates and suppressed viral load). To examine important temporal changes in psychological factors, mean changes will be calculated for HLC, FSSQ, MHC-SF, and SRBBS scores from the transfer baseline to 12 and 24 months post transfer. Additionally, between-group comparisons will be made using repeated-measures analysis of variance (ANOVA). Owing to multiple tests among the same subjects, an approximate type 1 error of .05 will be maintained either directly through the use of a technique designed to accommodate repeated-measures designs (e.g., RM-ANOVA), or through the use of post-hoc adjustment of *p* values (e.g., Bonferroni’s method).

Simultaneously, ACT will examine direct and indirect contribution of psychosocial factors on viral-load suppression and retention of study participants in both study arms through multiple mediation model analyses as recommended by Preacher and Hayes [45]. Mediation analyses are particularly useful in randomized control trials as they attempt to capture the effects or processes that occur after randomization. As noted by Preacher and Hayes, the multiple mediation model is preferred over the traditional simple mediation model [45]. Additional mediator/moderator models will also be explored in order to investigate the potential direct and indirect impacts of other ACT intervention components; these will include the use of peer-led support groups during the pre- and post-transfer period, and the relative impact of case management support on retention rates and viral-load measures.

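### The psychosocial secondary outcome is named as a proportion, but the hypothesis and the only stated analysis use continuous scores, so no analysis in the article estimates the outcome as named

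*Protocol article*

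**What the plan says.** All places are in the protocol article.

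- **Outcome measures** names the outcome as "Proportion of ALHIV demonstrating psychosocial wellbeing during study follow-up" and lists four questionnaires: HLC, MHC-SF, FSSQ and SRBBS.
- **Abstract, Methods** gives the secondary measures as "proportions of ALHIV achieving viral suppression and demonstrating increased psychosocial wellbeing and self-efficacy measured by psychometric tests".
- **Study objectives and hypotheses** expects the intervention arm to show "higher scores on psychometric testing indicating better psychosocial wellbeing".
- **Statistical analysis**, for secondary objective 2, states that "mean changes will be calculated for HLC, FSSQ, MHC-SF, and SRBBS scores from the transfer baseline to 12 and 24 months post transfer". Arms are then compared by repeated-measures ANOVA. A type 1 error of about .05 is kept through that method or through adjusted p values such as Bonferroni's.
- **Timing.** Data collection and Outcome measures place the questionnaires at enrolment, at transfer (12 months after enrolment), and at 6, 12 and 24 months post transfer. Description of the ACT intervention starts the support group at enrolment and runs the alternating visits over the 12 months before transfer.

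**The concern.** A proportion with a given state and a mean score are different summaries, and a result for one is not a result for the other. The two sections that tell a reader what will be reported call this outcome a proportion. The two that say what is hypothesised and analysed call it a score. If the article is followed as written, the planned analysis will be completed and the outcome as named will still have no estimate. A reader of the results could not tell which quantity is the pre-stated secondary outcome.

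The two definitions also differ from each other. Outcome measures describes a state (having wellbeing), while the Abstract describes a change ("demonstrating increased psychosocial wellbeing and self-efficacy measured by psychometric tests").

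A linked matter arises once the outcome is restated as a score. The analysis takes its baseline at transfer, and by then the intervention arm has had a year of support group and coordinated visits.

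**Working it through.** The article states no figure for this outcome, so there is nothing to reproduce. The check sets the sections side by side.

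**1. Type of outcome**

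| Place | Summary |
|---|---|
| Abstract, Methods | Proportion, of increased wellbeing |
| Outcome measures | Proportion, of wellbeing as a state |
| Study objectives and hypotheses | Higher scores |
| Statistical analysis | Mean score changes on four scales; repeated-measures ANOVA |

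Two places give a proportion and two give scores. The number of stated analyses that estimate or test a proportion for this outcome is zero.

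**2. Comparison with viral suppression**

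Viral suppression is also named as a proportion. Its event is defined ("Viral suppression is defined per the 2016 Nigerian national HIV guidelines as < 20 copies of HIV ribonucleic acid (RNA) per milliliter") and its analysis fits ("a one-way test of proportions will be conducted initially, followed by a Poisson count model"). Retention is handled in the same way, with an event definition and a test of proportions. Only the psychosocial outcome is named as one kind of quantity and analysed as another.

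**3. Does the score analysis give the proportion indirectly?**

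It does not. As an illustration, assume normal scores with SD 1 and a between-arm shift of 0.5 SD. The difference in the proportion above a cut-off c is Φ(c) − Φ(c − 0.5):

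- c = −1: 0.159 − 0.067 = 0.092, about 9 points
- c = 0: 0.500 − 0.309 = 0.191, about 19 points
- c = +1: 0.841 − 0.691 = 0.150, about 15 points

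The same mean difference matches quite different proportions, so the ANOVA result cannot stand in for the named outcome. The shift and the cut-offs are assumptions for illustration; the article gives none.

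**4. Baseline for the score analysis**

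Let a be the expected between-arm difference in score at transfer, and b the difference at 12 or 24 months post transfer. Randomisation makes the expected difference at enrolment 0.

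- Contrast in change from transfer: b − a.
- Contrast at follow-up, adjusted for the enrolment score: b.

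If the intervention raises scores during the transition year and the gain is held, then b = a and the change contrast is 0 although the intervention worked. The objective compares the whole intervention with usual care, and that comparison is b. The article does not say which time points enter the ANOVA. The argument therefore applies as far as arms are compared on change from transfer, which is the only change the section names.

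The enrolment score is available: the text and Table 1 both schedule a psychosocial assessment then. Table 1 as it reads here shows none at 12 months, although the text does, so enrolment is also the only pre-transfer measurement on which the two agree.

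**The case against.** The strongest reply is that the objective, the hypothesis and the analysis all point to continuous scores on named scales at 12 and 24 months, published in advance and with error control stated. On that view the word proportion is a loose label in two places, and a responder result reported later would be visibly outside the plan. This largely stands, and it limits the point to reconciling the definition with the analysis.

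A reader might infer more than the article supports:

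- **That missing cut-offs or a missing rule for combining the scales are a fault.** An article commonly leaves these to the full protocol or the analysis plan, which are not at hand.
- **That a cut-off will be picked after seeing the data, with inflated false positives.** The article plans no search for cut-offs and no responder test.
- **That information is lost by dichotomising.** No stated analysis dichotomises these scales, so no loss arises under the plan as written.
- **That the time frames contradict each other.** The broad reference to follow-up is settled by the listed administrations and by the choice of 12 and 24 months in the objectives and the analysis.

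The reply does not remove the mismatch. Condensation does not explain it, because the same article matches definition and analysis for retention and for viral suppression. A cut-off held elsewhere would define the proportion, but the analysis stated here would still not use it.

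It is also fair to say that an enrolment covariate departs from the Statistical analysis section. That is a real change. It must be made openly in that section, for the reason given in the working.

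**Conclusion.** The point holds as an internal contradiction. The Abstract and Outcome measures define the psychosocial secondary outcome as a proportion, while the hypothesis and the only stated analysis treat it as continuous scores. No analysis in this article estimates the outcome as named.

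Its size is a matter of definition rather than of a number. It concerns one secondary outcome on four scales and affects neither the primary outcome nor the sample size. It should be corrected before outcome data are analysed, because it settles which quantity counts as the pre-stated result.

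The contradiction rests on the text alone. The baseline recommendation rests on two further points: the intervention runs for 12 months before the transfer measurement, which the article states, and the quantity of interest is the effect of the whole intervention, which the secondary objective implies.

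**What to change.** **Abstract and Outcome measures.** Replace the proportion with wording such as: score on each of the HLC, MHC-SF, FSSQ and SRBBS at 12 and 24 months post transfer, compared between arms. Label any responder proportion descriptive.

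**Statistical analysis.** Edit to match: compare the 12- and 24-month scores between arms with the enrolment score as covariate, in place of change from transfer. If the team also wants to describe what happens after transfer, change from transfer can stay as a descriptive summary. This section has to be edited together with the other two; otherwise the new definition would conflict with the analysis.

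Keeping the proportion would also be coherent, but only with a responder rule pre-specified for each scale and an analysis of proportions that allows for clustering. It would move away from the stated hypothesis, so the score version is the smaller change.

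**Cost.** Wording edits in three places and a slightly different model. No new data are needed, since enrolment scores are already scheduled in both arms.
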